**Methods/Design:**

This study is a pragmatic randomized controlled trial. Over 4 successive winters we will recruit 750 healthy children 1–5 years of age. Participating physicians are part of a primary healthcare research network called *TARGet Kids!*. Children will be randomized to the ‘standard dose’ or ‘high dose’ oral supplemental vitamin D for a minimum of 4 months (200 children per group). Parents will obtain a nasal swab from their child with each URTI, report the number of asthma exacerbations and complete symptom checklists. Unscheduled physician visits for URTIs and asthma exacerbations will be recorded. By May, a blood sample will be drawn to determine vitamin D serum levels. The primary analysis will be a comparison of URTI rate between study groups using a Poisson regression model. Secondary analyses will compare vitamin D serum levels, asthma exacerbations and the frequency of specific viral agents between groups.

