### Viral upper respiratory tract infection

Viral upper respiratory tract infections (URTI) are the most common infectious disease in North America [42]. URTI is the most common reason for emergency department visits and unscheduled outpatient visits in Canada comprising 10% of emergency department visits for children under 10 years of age [2,43]. Preschoolers have the highest incidence of URTI of any age group, occurring 1–2 times per month per child during the winter and higher among children who attend daycare [42,44-49]. Influenza, RSV and adenovirus, which collectively comprise 25% of respiratory infections in children, are the most common viruses that lead to febrile illness, acute otitis media, outpatient visits and hospitalization [44,50]. Roughly 50% of preschoolers with URTI are brought to medical attention resulting in an additional outpatient physician visit every 2 to 3 months during the winter with 1% requiring hospitalization [44,51]. Several groups have estimated the direct and indirect costs of URTI in preschoolers to be between $261 and $276 per URTI with influenza being the most costly virus, contributing $809 per URTI [45,51]. The collective cost of URTI in children under 5 years of age has been estimated to be $1.8 billion annually in the US [52]. Evidence supporting a causal connection between low vitamin D serum levels and URTI comes from multiple sources.

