### Sample size

The sample size was based on asymptotic methods for a likelihood ratio test assuming a Poisson distributed outcome and was confirmed by simulation studies. All sample size and power calculations assume a 5% Type I error probability (two-sided). If we assume an average of one URTI per month during a minimum of 4 winter months [42,44-49] among children receiving the standard dose of vitamin D, we would therefore expect an average of four URTI per child over the winter. A sample size of 300 per group would give 90% power to detect a reduction in the average number of URTI per winter of one URTI. We believe that, even one fewer URTI over the winter would be a clinically important outcome, especially to families with young children. Although the study is not powered to detect reductions of specific kinds of infections, a conservative estimate is that at least 25% of children will have one of RSV, adenovirus or influenza which collectively result in the greatest burden of illness in this population [44,50], this sample size gives 80% power to detect a 50% absolute reduction in this composite outcome. Preliminary *TARGet Kids!* data suggests an 80% retention rate [107,112]; therefore, to accommodate a 20% loss to follow-up, 375 children will be recruited to each group (750 total).

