### Statistical analysis

Baseline characteristics will be summarized by appropriate descriptive statistics. Although randomization is expected to balance the covariates, variables that demonstrate, by chance, a potentially clinically meaningful imbalance, will be considered as possible adjusting covariates.

All outcomes will be analyzed following the *intention-to-treat* principle [113]. The primary analysis of the primary outcome will assess the effect of vitamin D supplementation on laboratory-confirmed URTI. Mean URTI rates (per child) will be computed for each group. A Poisson regression model will be used to make the statistical comparison between the groups. *Variable length of follow-up time* will be accounted for by using a suitable offset (logarithm of observation duration) in the Poisson model. If there is evidence of overdispersion, a negative-binomial model may be considered. The secondary analysis of the primary outcome will use survival methods to examine time to first URTI and the Andersen-Gill extension of the Cox model to analyze recurrent URTI events [114]. The rationale for conducting the trial over four seasons is to increase the chance of a sufficiently active viral season to assess a protective effect of the intervention. This will also allow us to examine the consistency of the effect over the four seasons as strains of viruses vary from year to year.

Analysis of secondary outcomes will use standard methods for continuous data (i.e., vitamin D level) using means, ANOVA and linear regression with and without adjustment for baseline group differences. The incidence of binomial secondary outcomes such as specific viral infections will be summarized descriptively. Since the incidence of some infections may be low, logistic regression analyses will only be performed to assess the treatment effect when there are sufficient events (over 30). Subgroup analyses will be conducted for children with asthma. Frequency of asthma exacerbations will be analyzed using the same methods as those used for the primary outcome.

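### The power statement for the RSV, adenovirus or influenza composite gives an impossible effect (a 50-point fall from 25%), and its 80% does not fit a 50% relative reduction either

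*Protocol article*

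**What the plan says.** The Sample size section of the Protocol article fixes a two-sided 5% Type I error for all its power calculations. It sets the trial size from the primary outcome: "A sample size of 300 per group would give 90% power to detect a reduction in the average number of URTI per winter of one" infection. That number is raised to 375 recruited per group to allow for 20% loss.

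The same section then turns to the viruses said to cause the greatest burden. After noting that the study is not powered for specific kinds of infection, it says that "a conservative estimate is that at least 25% of children will have one of RSV, adenovirus or influenza", and concludes that "this sample size gives 80% power to detect a 50% absolute reduction in this composite outcome". The sample size meant is the 300 per group just given. The test behind the 80% is not named.

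The Statistical analysis section adds: "The incidence of binomial secondary outcomes such as specific viral infections will be summarized descriptively". Logistic regression is kept for outcomes with more than 30 events.

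**The concern.** The assumed risk and the detectable effect stand in one sentence and cannot both be right. Subtracting 50 percentage points from 25% leaves a negative proportion. The obvious repair is to read the reduction as relative, but a halving of a 25% risk is a large effect for 300 per group, and 80% looks too low for it.

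What is at stake is interpretation. Influenza, adenovirus and RSV are named under the secondary objectives. A reader facing a null or borderline result on them would turn to this sentence to learn what size of effect the trial could have detected. As written, it gives no usable answer.

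**Working it through.** **Inputs**, all from the Sample size section: n = 300 per group; two-sided alpha = 0.05 (z = 1.96); standard-dose risk p1 = 0.25; stated power 80%; stated effect a 50% absolute reduction.

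**1. The statement as written.** p2 = 0.25 − 0.50 = −0.25. This is not a proportion, so no power can be calculated.

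**2. Read as a 50% relative reduction.** p2 = 0.125, difference d = 0.125, mean risk 0.1875. For the two-proportion test:

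power = Φ{ [d − 1.96·√(2·p̄(1−p̄)/n)] / √([p1(1−p1) + p2(1−p2)]/n) }

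- Null standard error: √(2 × 0.1875 × 0.8125 / 300) = 0.03187; times 1.96 = 0.06246.
- Alternative standard error: √((0.1875 + 0.109375) / 300) = 0.03146.
- (0.125 − 0.06246) / 0.03146 = 1.988, so power = 97.7%.

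The stated 80% is not reproduced. The same formula solved for 80% power gives 152 per group.

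**3. Does another test give 80%?** The test is not named, so the alternatives below were tried for 25% against 12.5%, at 300 per group and two-sided 5%.

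| Method | Power |
|---|---|
| Unpooled, or arcsine | 97.8% |
| Continuity-corrected | 97.0% |
| Fisher exact | 97.2% |
| Log odds ratio, Wald | 97.1% |
| Poisson log-rate, Wald | 93.4% |

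The Poisson figure takes 0.25 and 0.125 events per child. The expected counts are 75 and 37.5, the standard error of the log rate ratio is √(1/75 + 1/37.5) = 0.200, and ln 2 / 0.200 − 1.96 = 1.506.

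Two changes of input do not help. Halving the odds instead of the risk (25% to 14.3%) gives 91.2%. Counting all 375 recruited per group gives 99.3%.

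**4. Does a higher base rate help?** The 25% is stated as a lower limit. On the two-proportion test, 30% against 15% gives 99.3%, and 50% against 25% gives over 99.9%. A genuine 50-point fall becomes possible only when the risk is at least 50%; from 60% or 75% it would be detected with power of about 100%. Raising the base rate moves the result further from 80%.

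**5. What 80% power does correspond to.** With p1 = 0.25 and n = 300, solving the formula in step 2 gives p2 = 0.158. That is 25 − 15.8 = 9.2 points absolute, or 9.2/25 = 37% relative. A fall to exactly 16% has 78.1% power and a fall to 15% has 86.7%.

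**The case against.** The strongest reply is that nothing depends on this figure. The number of children comes from the primary infection count. The sentence opens by saying that the study is not powered for specific infections. The composite appears only in the Sample size section, and specific viral infections are to be described first and modelled only when events suffice. On the natural relative reading the article understates its power, so nobody is led to an undersized trial. All of this stands and keeps the point minor. It does not make the sentence correct: having disclaimed power for specific infections, the article still makes a numerical claim for the composite.

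A second reply is that 98% is itself conditional, because the test is not named. That also stands, and the result is best given as about 93% to 98% for a halving of risk. No part of that range is near 80%.

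A reader might infer two stronger things, and the documents do not support either.

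- **That the 25% contradicts the Background.** The Background says "Influenza, RSV and adenovirus, which collectively comprise 25% of respiratory infections in children", which is a share of infections, whereas the Sample size section speaks of children. If that share applied to the plan's four infections per child, it would mean 4 × 0.25 = 1 such infection per child, or 1 − e^(−1) = 63% of children with at least one under a Poisson assumption. But 63% satisfies a stated lower limit of 25%, so there is no contradiction. The conversion also rests on assumptions that the article does not make. All that remains is a request to confirm the unit.
- **That the 80% is left over from a smaller trial**, since the abstract still mentions 200 children per group. No passage links the two, and the match depends on the test chosen. For 25% against 12.5%, 160 evaluable per group (200 less 20%) gives 82% on a two-proportion test but about 72% on a Poisson Wald test. With 200 per group the figures are 89.6% and 80.8%. The origin of the 80% cannot be established from the article.

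**Conclusion.** The sentence is wrong on both readings. Taken literally, the effect cannot occur at the assumed 25%. Taken as a 50% relative reduction, power at 300 per group is about 98% (two-proportion test) or about 93% (Poisson log-rate Wald test), so the stated 80% is too low by roughly 13 to 18 percentage points. These figures assume 300 evaluable children per group, two-sided 5%, and a standard-dose risk of exactly 25% per child; a higher risk would widen the gap.

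Severity is minor. The error concerns a secondary composite, it does not touch the size set for the primary outcome, and it gives no ground for saying that the trial is too small for this composite.

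**What to change.** Reword the sentence and name the test. For example: with a 25% risk in the standard-dose group, 300 evaluable children per group give 80% power (two-proportion test, two-sided 5%) to detect an absolute reduction of about 9 percentage points (25% to about 16%, 37% relative), or about 98% power for a 50% relative reduction. If a Poisson model is intended for the composite, quote the figure for that model instead (about 93% for a halving, on a Wald test).

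At the same time, confirm that the 25% means children with at least one such infection. If it was meant as a share of infections, derive the risk per child and recompute.

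The cost is one reworded sentence. The sample size, conduct and primary analysis do not change.

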### Statistical analysis

Baseline characteristics will be summarized by appropriate descriptive statistics. Although randomization is expected to balance the covariates, variables that demonstrate, by chance, a potentially clinically meaningful imbalance, will be considered as possible adjusting covariates.

All outcomes will be analyzed following the *intention-to-treat* principle [113]. The primary analysis of the primary outcome will assess the effect of vitamin D supplementation on laboratory-confirmed URTI. Mean URTI rates (per child) will be computed for each group. A Poisson regression model will be used to make the statistical comparison between the groups. *Variable length of follow-up time* will be accounted for by using a suitable offset (logarithm of observation duration) in the Poisson model. If there is evidence of overdispersion, a negative-binomial model may be considered. The secondary analysis of the primary outcome will use survival methods to examine time to first URTI and the Andersen-Gill extension of the Cox model to analyze recurrent URTI events [114]. The rationale for conducting the trial over four seasons is to increase the chance of a sufficiently active viral season to assess a protective effect of the intervention. This will also allow us to examine the consistency of the effect over the four seasons as strains of viruses vary from year to year.

Analysis of secondary outcomes will use standard methods for continuous data (i.e., vitamin D level) using means, ANOVA and linear regression with and without adjustment for baseline group differences. The incidence of binomial secondary outcomes such as specific viral infections will be summarized descriptively. Since the incidence of some infections may be low, logistic regression analyses will only be performed to assess the treatment effect when there are sufficient events (over 30). Subgroup analyses will be conducted for children with asthma. Frequency of asthma exacerbations will be analyzed using the same methods as those used for the primary outcome.

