**ASSESSMENTS:**					
**Baseline survey data**	X	X			
**Anthropometrics**		X			
**25-hydroxyvitamin D serum level**			X	X	
**Laboratory-confirmed URTI**			X		
**Asthma exacerbations**			X		
**Follow-up survey data**				X	
**ANALYSIS**					X

Concomitant interventions prohibited include over-the-counter multivitamins which contain vitamin D, over-the-counter vitamin D preparations and prescription vitamin D. As this is a pragmatic trial, no specific strategies are introduced to improve adherence. To monitor adherence at the end of the trial, parents are asked to return bottles and the amount of vitamin D administered is calculated based on the volume of solution remaining [94]. No specific criteria are being used for discontinuation or modification of the interventions, as the doses of vitamin D are within the safe and recommended dosages for children [70].

Block randomization occurs by study site with blocks of varying sizes to ensure that group sizes are similar at the end of each block [88]. This is particularly important in a study of vitamin D and URTI, as date of enrolment (time) may be an important covariate. Sequence generation stratified by practice site was performed centrally at the Applied Health Research Centre (AHRC) at St. Michael’s Hospital using a computer random number generator; KT (biostatistician and co-author) generated the allocation sequence. Parents, attending physicians, laboratory personnel, and study personnel conducting the outcome assessments, data analysts and investigators are blind to the group allocation. Allocation concealment is achieved by having the Pharmacy Department prepare the vitamin D preparations in sealed, serially numbered bottles identical in appearance and weight, with the drops similar in consistency and taste. Group allocation will be concealed until the final data analysis is performed.

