### Recruitment and retention

Since June 2008, over 4500 children age 1–5 years have been recruited through *TARGet Kids!* practices with collection of questionnaires (demographics, lifestyle factors) and anthropometric measures (height, weight and waist circumference). Since December 2008 venous blood samples have been collected from over 2500 children [107]. *TARGet Kids!* is now operating out of seven sites with over 100 children per month being recruited with phlebotomy. Therefore, recruitment of 750 children in September through November over 4 consecutive seasons for this study is feasible.

We expect that there will be a different spectrum of infections as respiratory virus incidence, distribution and severity tend to vary from year to year.

Strategies to achieve adequate recruitment include approaching eligible subjects during a well-child visit. Lists of children scheduled for a well-child visit are reviewed in advance. An information package is mailed to each family 2 to 4 weeks prior to the visit inviting them to participate. This allows parents time for consideration in advance and reduce coercion to participate. Parents are approached in person by the research assistant while registering for the clinic visit. At the initial visit, baseline survey data, anthropometric measures, and baseline vitamin D serum level are collected.

Strategies for retention include a monthly telephone call to encourage collection of nasal swabs and completion of symptom checklists. Every reasonable attempt is made to locate patients at follow-up. Topical anesthetic cream (EMLA or Ametop) is offered to minimize discomfort from venipuncture. Blood is drawn in the primary care physician’s office negating the need to attend a separate laboratory visit. Parents who have moved out of district are offered to visit The Hospital for Sick Children for repeat laboratory testing. Should these efforts fail to obtain a blood sample, a home visit for phlebotomy is offered. This is expected to occur in less than 10% of subjects.

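### Covariate adjustment follows observed imbalance, and the described primary model names neither site nor winter: this leaves avoidable model discretion and can cost precision once overdispersion is corrected

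*Protocol article*

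**What the plan says.** On covariates, the opening paragraph of the Statistical analysis section states that "variables that demonstrate, by chance, a potentially clinically meaningful imbalance, will be considered as possible adjusting covariates".

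On the primary model, the same section says: "A Poisson regression model will be used to make the statistical comparison between the groups". Unequal follow-up is "accounted for by using a suitable offset (logarithm of observation duration) in the Poisson model". There is one fallback: "If there is evidence of overdispersion, a negative-binomial model may be considered". Season appears only as a check that the effect is consistent over the four winters. Continuous secondary outcomes are to be analysed both with and without baseline adjustment, and asthma exacerbations take the primary outcome's methods.

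On design, the randomisation paragraph of the Intervention section says "Block randomization occurs by study site with blocks of varying sizes" and "Sequence generation stratified by practice site was performed centrally". It explains that blocking matters here because "date of enrolment (time) may be an important covariate". The Recruitment and retention section expects that "respiratory virus incidence, distribution and severity tend to vary from year to year".

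**The concern.** The design and the described analysis do not line up. The protocol stratifies by site, gives enrolment time as the reason for blocking and expects incidence to move from year to year. Yet the comparison it describes contains a group term and an offset, and its only stated rule for adding covariates depends on which variables happen to differ between arms.

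Two things are at stake. First, a covariate is worth adjusting for because it predicts the outcome, not because it is out of balance. A rule triggered by imbalance, with no list, no threshold and no primary estimate named, leaves the model open until grouped baseline data have been seen. Second, site and winter effects left out of the model show up as extra-Poisson variation. If that is then corrected for, the arm comparison carries a standard error that includes variation which the blocked design has already balanced out.

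**Working it through.** **Inputs from the protocol.** Seven sites, four winters, blocks of varying size within site, control mean of 4 infections per child, 300 children per group after losses, two-sided 5% test. The protocol gives no between-site or between-winter variance, so these are assumed below and varied.

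**Effect size used.** The plan states 90% power for a fall from 4 to 3 with 300 per group. Under its Poisson assumption the need is n = (1.96 + 1.2816)² × (4 + 3) / 1² = 73.6, so 74 per group. With 300 per group, 90% power corresponds to a fall of about 0.51. That mismatch is a separate matter. Here it only explains why the checks use 4 to 3.5 (rate ratio 0.875).

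**How often the imbalance rule would fire.** Assume a threshold of 0.1 SD. With 300 per arm the standardised difference has SE √(2/300) = 0.0816, so one variable exceeds 0.1 with probability 0.221 (z = 1.225).
- Six independent variables: 1 − 0.779⁶ = 78%. Simulation gave 77-79%.
- About 20 variables, roughly the number in the Participants section: 1 − 0.779²⁰ = 99%. At a threshold of 0.2 SD (probability 0.0143 each) it is 25%.

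So whether the rule fires depends heavily on a threshold the plan does not give.

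**Site and winter, plain Poisson standard error.** Simulation: 2,000 trials per scenario, 600 children, 7 sites, 4 winters, blocks of 2/4/6 within site. With site/winter SDs of 0.2/0.3 and no residual overdispersion, the SE is 0.0414 without the two terms and 0.0414 with them; power is 89.7% and 89.6%. With residual overdispersion, power is 79.2% and 79.5%, but plain Poisson then rejects a true null in about 24% of trials, so those figures are not usable.

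**Site and winter, overdispersion-corrected standard error.** The SE is multiplied by √φ, where φ = Σ(y − μ)²/μ ÷ (n − p). In the first row (no residual overdispersion), omitting the terms alone gives φ of about (0.0488/0.0414)² = 1.39. The other rows add residual heterogeneity: gamma with dispersion 0.25, plus prognostic covariates with log-rate SD 0.3.

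| Site/winter SD | SE without | SE with | Cut | Power without | Power with |
|---|---|---|---|---|---|
| 0.2/0.3, no residual | 0.0488 | 0.0414 | 15% | 81% | 89% |
| 0.1/0.2 | 0.0669 | 0.0640 | 4% | 52% | 55% |
| 0.2/0.3 | 0.0709 | 0.0638 | 10% | 47% | 57% |
| 0.3/0.5 | 0.0798 | 0.0630 | 21% | 38% | 55% |

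A separate simulation with robust standard errors (500 null trials per scenario, SDs 0.2/0.3) gave adjusted/unadjusted ratios of 0.84, 0.88 and 0.91 at mean 4, that is, cuts of 16%, 12% and 9%. At mean 1 the ratios were 0.96 and 0.97, cuts of 3-4%.

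**Calibration.** The estimates themselves hardly change in spread: 0.0671 without and 0.0667 with the terms in the third row. Blocking within site has already balanced site and enrolment time, so what changes is the reported SE. Without the terms, the corrected test is conservative where site and winter effects exist (type I error 2.5% to 4.2%). With them, the scaled SE held 4.9% without residual overdispersion, but gave 6.4% (0.2/0.3) and 7.2% (0.3/0.5) with it. A single scale factor therefore flatters the adjusted model in the lower rows. Set against the actual spread of the adjusted estimates (0.0666, 0.0667, 0.0682), the cuts in the last three rows become 0.4%, 6% and 15%.

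**Type I error of the imbalance rule.** Applied mechanically at 0.1 SD with six covariates, it gave 2.6% to 5.2%. With no true heterogeneity, picking the most favourable of three models gave 5.6% against 5.0%.

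**The case against.** The strongest reply is that site and winter are not named rather than excluded. This is a condensed article, its analysis plan is not at hand, and listing stratification terms is normal content for that plan. That stands: a reader might infer that the primary model deliberately omits both, and the text does not say so.

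A reader might also infer that the primary estimate itself will depend on the data. The imbalance sentence sits with the baseline summaries, speaks of variables being considered, asks for clinical meaning rather than a significance test, and is not tied to the primary model. The estimate may depend on it; the text does not show that it must. Blinding of analysts and investigators also limits steering towards one arm, though it does not fix the model.

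A third inference, that the test is invalid, fails on the figures above. Omitting the terms makes a corrected test conservative, and the imbalance rule did not inflate type I error. Nor is lost precision a general result, because under the plain Poisson model that the protocol names first it is nil.

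What the reply does not remove is the stated rule. It is an affirmative choice, not a gap left for another document, and it points at chance imbalance although the protocol itself identifies site and time as the factors that matter.

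**Conclusion.** The point holds as an avoidable weakness in model specification, not as an error that biases the trial. The stated adjustment rule leaves the model open and no estimate is named as primary. The described model does not name the randomisation stratum or the season.

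The precision at stake is conditional. It arises on the overdispersion-corrected branch that the plan allows, and omitted site and winter effects would themselves help to trigger that branch. At mean 4, assumed site/winter SDs of 0.1/0.2 to 0.3/0.5 give a reported SE about 4% to 21% smaller with both terms. Part of that comes from the scaling method, and less remains at each setting when judged by the actual spread of the estimates. The gain is about 3-4% at mean 1 and essentially nil with plain Poisson standard errors. All of these sizes rest on variances that the protocol does not give.

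**What to change.** Name site and winter as fixed factors in the primary model, whether Poisson or negative binomial, and state that this adjusted estimate is primary. If overdispersion is present, take the standard error from the negative binomial model or a robust estimator rather than from a single scale factor, given the calibration results above. Add at most a short list of named prognostic baseline variables that are fully collected, such as age, entered whatever their observed balance. Keep any imbalance-driven adjustment only as a labelled sensitivity analysis.

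The cost is (7 − 1) + (4 − 1) = 9 degrees of freedom out of about 600 children, and a change of analysis wording. Site, winter and age are already recorded. Baseline 25-hydroxyvitamin D needs a venous sample and may be missing for some children, so it should enter only with a stated way of handling missing values; otherwise the intention-to-treat set would shrink. The choice of further covariates is a matter of judgement; fixing the list in advance is what matters.

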### Outcomes and measures

The *primary outcome* is the number of laboratory-confirmed viral URTIs per child over the winter months. Because of the wide variety of respiratory viruses and URTI illness presentations, signs and symptoms of viral URTI are non-specific and may not be reliably measured by parental report [95,96]. Therefore, in addition to parents of enrolled children completing a symptom checklist with each URTI (see Additional file 3: Symptom Checklist), parents are asked to obtain a nasal swab from their child. Nasal swabs done by parents have been shown to be as effective in detecting respiratory viruses as those obtained by health professionals but less invasive and better tolerated [97]. Parents are instructed to place the swab in provided viral transport media and refrigerate until couriered to the study laboratory (Mount Sinai Services) within 24 hours [44,98]. Respiratory viruses are identified using reverse transcriptase polymerase chain reaction (RT-PCR) technology. RT-PCR is performed on each sample which has a sensitivity of 95% and specificity of 100% for the identification of respiratory RNA viruses, which is more sensitive than viral culture and comparable to immunofluorescence [99]. Samples are tested for 18 common respiratory viruses including influenza A and B, adenoviruses, respiratory syncytial virus (RSV), picornaviruses (enteroviruses and rhinoviruses), coronovirus, metapneumovirus and parainfluenza virus using the ID-Tag™ RVP assay using the Luminex xMAP™ system (Cat# R019A0105, TM Bioscience Corp., Toronto, ON) [100]. This is the same assay and machine that is routinely used in the Ontario public health laboratories.

*Secondary outcomes* include parent reported URTI, specific viral agents that cause URTI (influenza, adenovirus and RSV), asthma exacerbations among children with asthma, physician-diagnosed otitis media and pneumonia, emergency department visits and hospitalizations, collected by monthly telephone call and confirmed by review of the child’s clinic medical record. Follow-up 25-hydroxyvitamin D serum level is measured to determine the vitamin D dose vs. serum response relationship. Finally, change in 25-hydroxyvitamin D serum level from baseline is determined to document that an improvement in health outcomes is mediated through an increase in 25-hydroxyvitamin D serum level.

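### The primary Poisson test leaves the response to overdispersion optional, so its 5% type I error may not be held if counts are overdispersed and the switch is not taken

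*Protocol article*

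**What the plan says.** The primary outcome is the "number of laboratory-confirmed viral URTIs per child over the winter months" (Outcomes and measures). It is a count of recurrent events per child.

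For the test, the Statistical analysis section says: "A Poisson regression model will be used to make the statistical comparison between the groups". Unequal follow-up enters through an offset, the log of observation time. On extra-Poisson variation there is one sentence: "If there is evidence of overdispersion, a negative-binomial model may be considered". The section names no robust or scaled variance, and it says asthma exacerbations will be analysed by the same methods as the primary outcome.

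The Sample size section works at a two-sided 5% level and rests on "asymptotic methods for a likelihood ratio test assuming a Poisson distributed outcome and was confirmed by simulation studies".

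**The concern.** Ordinary Poisson standard errors are right only if, given arm and follow-up time, the variance of the counts equals their mean. The article gives three reasons to doubt this:

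- Background (Viral upper respiratory tract infection) puts the winter rate in preschoolers at one to two per month, and higher in daycare. The primary model as described has no covariate beyond the time offset.
- Recruitment and retention expects virus incidence to vary from year to year, and four seasons are pooled.
- An infection enters the primary outcome only if a parent takes a swab, and monthly calls are needed to encourage this. Families who differ in how reliably they swab add variation between children.

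If the variance exceeds the mean and the Poisson standard errors are kept, the confidence interval for the primary comparison is too narrow and the null is rejected too often. Because the negative-binomial model is only something to be considered, and no criterion is given, the choice between two p-values can also be made with both in view.

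**Working it through.** **Inputs.** Two-sided 5% level, 300 analysed per group, and means of 4 versus 3 URTI per child (Sample size). Follow-up is 4 to 8 months (Intervention). The variance/mean ratio φ is not given anywhere, so it is an assumption and is shown as a range.

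**Type I error if Poisson is kept.** Under the null, the true standard error is √φ times the Poisson one. The Poisson z statistic then has variance φ, and

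type I error = 2[1 − Φ(1.96/√φ)].

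The simulated column uses gamma-Poisson counts with mean 4, 300 per group, equal follow-up, 6,000 trials and the Poisson likelihood ratio test.

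| φ (assumed) | 1.96/√φ | Formula | Simulated |
|---|---|---|---|
| 1.0 | 1.960 | 5.0% | 5.2% |
| 1.2 | 1.789 | 7.4% | 6.6% |
| 1.5 | 1.600 | 11.0% | 10.9% |
| 2.0 | 1.386 | 16.6% | 16.3% |
| 3.0 | 1.132 | 25.8% | 26.1% |

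The first row reproduces the plan's own 5% when the counts really are Poisson.

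**What the article's own rates could imply.** Treat one to two per month as a spread of rates between children followed for T months. This is an illustration only, since the range may describe averages rather than individual children, and it refers to all URTI rather than laboratory-confirmed ones. The mean count is 1.5T, and φ = 1 + T²·var(rate)/(1.5T).

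- Uniform spread, var = 1/12: φ = 1 + T/18, which is 1.22 at 4 months and 1.44 at 8. Type I error is 7.6% to 10.3%.
- Half the children at 1 and half at 2, var = 0.25: φ = 1 + T/6, which is 1.67 to 2.33. Type I error is 12.9% to 20.0%.

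**The opposite direction.** A new URTI needs at least three symptom-free days after the last one (Outcomes and measures). That spaces events out and lowers the variance. Simulating an assumed 10-day gap (7 days of illness plus 3) at about four illnesses per winter, with identical children and 60% swabbing, gave φ = 0.68. Then 1.96/√0.68 = 2.38 and the type I error is 1.7%, which is conservative. With identical illness rates but assumed swabbing of 90% in half the families and 30% in the rest, φ was 1.20.

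**Remedies.** At mean 4 and φ from 1 to 3, negative binomial from the start gave simulated type I error of 4.6% to 5.2%. A binding rule (Pearson dispersion test at 5%, then negative binomial if positive) gave 4.6% to 5.6%. Robust standard errors were not simulated. Their validity for φ above or below 1 at 300 per group rests on large-sample theory.

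**Power after the change.** For 4 versus 3 with 300 per group, power = Φ[ln(4/3)/√(φ(1/4 + 1/3)/300) − 1.96]. The result is above 99.99% at φ = 1, 99.6% at φ = 2 and 96.5% at φ = 3. The article states 90% for these inputs, which does not reproduce: 90% power needs only (1.960 + 1.282)² × 7/1² = 73.6, so 74 per group. That discrepancy is a separate matter. Here it shows only that, on the stated 4 versus 3, a wider interval needs no extra children.

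**The case against.** The plan foresees overdispersion and names a standard remedy, so every figure above 5% describes the branch in which that remedy is not used. No dispersion value is given, and the episode rule could make the test conservative instead. This stands: the inflation is conditional and should not be stated as fact.

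A full analysis plan, not at hand, may bind the choice. That is possible. However, the article does state a rule for its primary test, and the rule it states is optional.

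Analysts and investigators are blind to allocation until the final analysis. This limits choosing a model to favour one arm. It does not prevent choosing by significance between coded groups.

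Four stronger readings are tempting, and the documents do not support them:

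- *A data-dependent switch is itself a defect.* The binding switch held close to 5% in simulation. The weakness is the optional wording with no criterion.
- *Type I error of 33%.* A variance inflation of about 4 would make the stated 90% power come out, and would give this figure. But the Sample size section assumes a Poisson outcome, and 90% comes out equally from 1 versus 0.75 events per child with no overdispersion. The power mismatch is not evidence about dispersion.
- *Site differences as a source of overdispersion.* The article uses site to stratify randomisation and does not say that URTI risk differs by site.
- *No robust variance for "the Andersen-Gill extension of the Cox model to analyze recurrent URTI events".* This is a secondary analysis, and its variance estimator is a detail commonly left to the analysis plan.

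**Conclusion.** The point holds in conditional form. As written, the plan allows ordinary Poisson standard errors to decide the primary comparison even when overdispersion has been found. If that happened, the type I error would be about 7%, 11%, 17% or 26% at assumed variance/mean ratios of 1.2, 1.5, 2 or 3. If the counts were underdispersed it would fall below 5%. What the article says about infection rates, seasons and parent-collected swabs makes extra variation likely, but neither its size nor its direction is settled by the documents.

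This should be fixed, because it bears on the trial's main test. It is not a fatal flaw, since the plan already recognises the issue and names a workable remedy.

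**What to change.** Replace the optional sentence with a commitment. Preferred: the primary analysis is Poisson regression with log observation time as offset and robust (sandwich) standard errors, with a negative-binomial model as sensitivity analysis. This is valid whether the counts are over- or underdispersed. Acceptable alternatives are negative binomial as primary from the start, or a mandatory switch to it on a stated criterion. Apply the same rule to asthma exacerbations.

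The text change is one sentence. The statistical cost is a wider interval if counts are overdispersed, by about √φ: 22% at 1.5 (√1.5 = 1.22) and 41% at 2 (√2 = 1.41). That is the honest width, not a loss caused by the method. If the counts are Poisson, essentially nothing is lost.

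On the stated 4 versus 3 with 300 per group, no added sample is needed. Negative-binomial power stays at or above 90% up to a dispersion parameter of about 0.89, which is a variance/mean ratio of 1 + 4 × 0.89 = 4.6 at mean 4. If the design was really built on 1 versus 0.75 events per child, this margin would be gone, so the basis of the 90% should be confirmed at the same time.
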